### Randomization and Sample Size Calculation

Enrolled LTBI participants linked to the same index case will be defined as a cluster [14,15], with an assumed average cluster size of 4 participants. Cluster-level randomization will be triggered when ≥1 eligible participant is enrolled within a cluster. Randomization sequences will be pregenerated by the study statistician using SAS (version 9.4; SAS Institute Inc) and will not be accessible to any personnel involved in enrollment, assignment, or intervention delivery. Designated personnel will perform centralized randomization via the interactive web response system. Randomization results will be relayed to the respective site investigators. This is an open-label study, and all participants within the same cluster will receive identical group assignments. To address intercenter heterogeneity, a 2-stage randomization strategy will be applied: in the first stage, stratification by study site will balance baseline characteristics across centers; in the second stage, permuted block randomization (block size=4) within each site will ensure immediate group balance during participant enrollment.

On the basis of surveillance data from China’s National Tuberculosis Control Program, we estimate that the 2-year cumulative active TB incidence among LTBI participants will be 7% [16,17]. Both the 3HR and 1H_3_P_3_ regimens are assumed to have 70% protective efficacy (ie, reducing the 2-year cumulative incidence of active TB into 2.1%).

The intracluster correlation coefficient (ICC) was incorporated into calculations. A systematic review reported ICC values of 0.028 (range 0.0005‐0.21) for school-based clusters [15], while the National Institutes of Health Pragmatic Trials Collaboratory suggested a range of 0.01 to 0.05 [18]. Therefore, we adopted a conservative ICC estimate of 0.05 for this study.

Using these parameters and a prespecified noninferiority margin of a 20% relative reduction in protective efficacy, a total of 396 clusters (n=1584 participants) per treatment arm are required to achieve 80% power at a 1-sided *α*=.05. This sample size is calculated to satisfy the clinically meaningful noninferiority margin, accounting for the cluster randomized design (ICC=0.05, average cluster size=4). Accounting for a 10% attrition rate to mitigate the impact of loss to follow-up on statistical power and outcome validity, each arm will enroll 1760 participants.

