### Statistical Analysis

Statistical analyses will be performed using SAS and R (R Foundation for Statistical Computing). Multiple imputation will be conducted to handle missing data, with additional inverse probability weighting applied for the nonintervention cohort to adjust for potential attrition bias. Continuous variables will be summarized as mean (SD) or median (IQR), as appropriate. Categorical variables will be summarized as counts and percentages.

The primary analysis will assess the noninferiority of the 1H_3_P_3_ regimen compared to the 3HR regimen in preventing active TB over the 24-month follow-up period, and the primary end point is the composite of bacteriologically confirmed or clinically diagnosed active TB. To account for the cluster randomized design and the inherent correlation within clusters, we will use a Cox proportional hazards regression model with shared frailty terms and exact likelihood estimation. Noninferiority of the 1H_3_P_3_ regimen relative to the 3HR regimen will be concluded if the analysis demonstrates that the 1H_3_P_3_ regimen does not experience a ≥20% relative reduction in protective efficacy for preventing active TB over the 24-month follow-up period. To enhance precision and address potential baseline imbalances despite randomization, the model will adjust for key prespecified covariates, such as age, sex, BMI, characteristics of the index case (smear or cavitation status), and cluster size. Outcomes will be assessed via 2 prespecified analyses with explicit definitions: the modified intention-to-treat population includes all randomized participants who received at least 1 dose of the study medication, analyzed by the assigned treatment group regardless of subsequent protocol deviations or treatment discontinuation; the per-protocol population includes all randomized participants who completed ≥90% of scheduled doses within 110% of the planned treatment duration without major protocol deviations (including use of prohibited concomitant anti-TB medications, enrollment despite exclusion criteria, or unblinding to outcome assessors). Prespecified subgroup analyses will examine treatment effect heterogeneity by age (13-17 years vs ≥18 years) and index case features (smear or cavitation status), tested through interaction terms in Cox models (interaction *P*<.10).

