## Results

Recruitment started in September 2023. By the end of December 2025, a total of 2478 participants, comprising 627 index cases, had been enrolled, and the recruitment is estimated to continue until September 2026. Data analysis will commence after the 2-year follow-up period, and the results are expected to be published by March 2029.

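### The sample size uses the equal-cluster design effect of 1.15, so at the protocol's own ICC the stated 80% power is somewhat too high once cluster sizes vary

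*Protocol article*

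**What the plan says.** In the protocol article, Methods, section Randomization and Sample Size Calculation, a cluster is the set of enrolled infected participants linked to one index case, with an assumed mean of 4. The requirement is 396 clusters, or 1584 participants, per arm for "80% power at a 1-sided *α*=.05", "accounting for the cluster randomized design (ICC=0.05, average cluster size=4"). Ten per cent attrition raises this to 1760 per arm. No standard deviation or CV of cluster size is given.

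The same section sets the smallest possible cluster: "Cluster-level randomization will be triggered when ≥1 eligible participant is enrolled within a cluster". It calls the ICC of 0.05 conservative, citing a review value of 0.028 (range 0.0005 to 0.21) and a suggested range of 0.01 to 0.05.

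In the section Statistical Analysis, the shared-frailty Cox model adjusts for, among other things, "characteristics of the index case (smear or cavitation status), and cluster size". In the section Results, "a total of 2478 participants, comprising 627 index cases, had been enrolled" by the end of December 2025.

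**The concern.** The inflation factor 1+(m−1)×ICC assumes that every cluster has m members. For unequal clusters the usual form is 1+[(1+CV²)m−1]×ICC, which is larger whenever CV is above 0. In this trial size depends on how many class and dormitory contacts test positive, are eligible and consent, so it will vary. The covariate for cluster size shows that the plan expects this; the covariate does not itself inflate the variance.

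If the spread was left out, the effective sample size is smaller than the text implies and the confidence interval for the noninferiority comparison will be wider than planned. A regimen that is truly noninferior then has a greater chance of failing than the stated 20%. The validity of the analysis is not in question, because a frailty model accommodates unequal clusters.

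**Working it through.** **Inputs from the sample size section.** Incidence 7% untreated and 2.1% in both arms (70% efficacy); one-sided alpha 0.05; power 80%; ICC 0.05; mean size m = 4; attrition 10%. The CV is not given, so it is an assumption, shown here from 0 to 1.0.

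**Step 1: reproduce the printed size.** The protocol does not name its formula. A Farrington-Manning score test with a limit of 3.5% (efficacy falling from 70% to 50%, absolute margin 3.5 − 2.1 = 1.4 points) matches. The restricted estimates under the null are 3.008% and 1.608%, so the null and alternative standard deviation terms are 0.2121 and 0.2028:

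n = [(1.645×0.2121 + 0.842×0.2028)/0.014]² ≈ 1377.2 per arm

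1377.2 × 1.15 = 1583.8, i.e. 396 clusters of 4 = 1584, and 1584/0.9 = 1760. All three printed figures agree. The other standard formulas tried with the same inputs and the factor 1.15 did not match (for example 1493, 1653 and 1973 per arm). An allowance for unequal sizes would have given a larger number.

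**Step 2: allow for unequal sizes.** DE = 1+[(1+CV²)×4−1]×0.05, with effective size 1584/DE per arm:

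| CV (assumed) | DE | Effective n per arm | Power | Participants per arm for 80% |
|---|---|---|---|---|
| 0 | 1.15 | 1377 | 80.0% | 1584 |
| 0.5 | 1.20 | 1320 | 78.5% | about 1653 |
| 0.75 | 1.26 | 1255 | 76.6% | about 1739 |
| 1.0 | 1.35 | 1173 | 74.0% | about 1859 |

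Power reaches 78%, a loss of 2 points, at a CV of about 0.57.

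**Step 3: attrition by individual.** The table treats attrition as leaving 396 clusters of mean 4. If individuals drop out instead, 1760/4 = 440 clusters remain with mean size 1584/440 = 3.6. With m = 3.6, DE is 1.175, 1.231 and 1.31 at CV 0.5, 0.75 and 1.0, and power is 79.2%, 77.5% and 75.2%.

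**Step 4: the cited ICC of 0.028** (m = 4, 1584 analysed). DE is 1.112, 1.147 and 1.196 at CV 0.5, 0.75 and 1.0, and power is 81.2%, 80.1% and 78.6%. Setting DE = 1.15 gives CV² = (0.15/0.028 + 1)/4 − 1 = 0.589, so CV ≈ 0.77.

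**Step 5: the mean size.** 2478/627 = 3.95, in line with the assumed 4. This takes one cluster per index case. Only the spread is missing.

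**The case against.** The strongest reply is that the ICC already carries a reserve. The protocol took 0.05, the top of one cited range, over a reviewed value of 0.028, and at 0.028 the factor 1.15 absorbs a CV up to about 0.77. That arithmetic stands. But the section justifies 0.05 only against published ICC values and never as an allowance for unequal sizes. The other cited range reaches 0.21, where DE = 1+3×0.21 = 1.63 and power is about 67% even with equal clusters. The stated 80% is conditional on ICC 0.05, and at that value it does not allow for any spread.

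Second, the deciding figure is absent. A reader might infer that the trial has lost 5 points of power or more. That needs a CV approaching 1, and no section supports such a value. A shifted Poisson distribution with minimum 1 and mean 4 has a CV of 0.43 and, under efficient weighting, gives 79.0%. Moderate variation is compatible with the documents, and so is marked variation.

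Third, a reader might infer that the protocol claims clusters of exactly 4. It does not: it says average. Equal size is implied by the arithmetic, not asserted in the text.

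Fourth, whole-cluster attrition is the pessimistic case, as step 3 shows. The Cox model also uses follow-up before censoring, and covariate adjustment may add some precision that these figures do not credit.

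**Conclusion.** The point holds in a limited form. The printed size contains no allowance for unequal clusters although the design makes them unequal, so at ICC 0.05 and mean size 4 the stated 80% power is somewhat too high. The direction is firm at that ICC. The size is not: about 1.5 to 6 points for CV 0.5 to 1.0 with 1584 analysed in clusters of mean 4, about 1 to 5 points if attrition is individual, and under 2 points below a CV of about 0.57. An unconditional statement that the trial is materially underpowered for this reason is not supported.

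These figures rest on the 1.4-point margin that reproduces the printed size. The text states the margin as "a prespecified noninferiority margin of a 20% relative reduction in protective efficacy", which read literally takes efficacy from 70% to 0.8×70% = 56%, a limit of 7%×0.44 = 3.08% and a margin of 0.98 points. Under that reading, power at 1584 per arm is about 54% even with DE 1.15, and about 49% at CV 1.0. That mismatch is a separate and larger matter. The missing CV term lowers power under either reading.

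**What to change.** Compute the mean and CV of cluster size from the clusters already enrolled (627 index cases), pooled over arms and without outcome data. Count clusters as randomized, since the Discussion assigns contacts with several possible sources to the earliest index case, so clusters may be fewer than index cases. Replace 1.15 by 1+[(1+CV²)m−1]×ICC, and restate the power at the planned size for ICC 0.05 and 0.028, saying whether attrition is taken by cluster or by individual. Settle the margin in the same recalculation, so that the restated power refers to the rule that will be applied.

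The cost is a short calculation on data already held and a revised sentence or two. This correction requires no extra enrolment. The only downside is a slightly less favourable stated power.

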### Data Collection and Management

The trial workflow adheres to the SPIRIT (Standard Protocol Items: Recommendations for Interventional Trials) statement [19]. Site investigators and staff from each center will undergo centralized training to standardize protocols for participant screening, intervention delivery, follow-up procedures, end point adjudication, and AE documentation and management. Each participant will be assigned a unique anonymized identifier, accessible only to authorized personnel for monitoring purposes. Data will be prospectively captured on paper-based case report forms (CRFs) by on-site investigators or clinical research coordinators, followed by single-entry migration into a customized electronic data capture system. The electronic data capture platform enforces role-based access control to ensure confidentiality. Data integrity audits will be conducted monthly by the data management team. Upon trial completion, the central coordinating office will execute database locks, after which only 2 primary investigators and 1 independent statistician will retain access to the final analytic dataset.

For the primary end point assessment, investigators will perform symptom screening (eg, cough, fever, night sweats, weight loss, and hemoptysis) and physical examination to identify suspected active TB cases at each visit. Participants meeting clinical criteria will undergo confirmatory testing, including chest imaging (preferably chest CT), sputum culture, and sputum molecular testing (eg, GeneXpert MTB-RIF). All suspected cases will undergo centralized adjudication by an independent TB expert panel to confirm the diagnosis.

For secondary end points assessment, AEs will be documented in a dedicated CRF section, capturing event type, onset date, severity (graded according to Division of AIDS criteria), presumed causality, management, and resolution status. Medication adherence will be tracked through participant interviews, drug diary review, and pill counts; discrepancies will be resolved by prioritizing measured residual drug quantities. Survival status will be verified at each visit. Postdropout mortality ascertained through external sources will trigger outcome reclassification from “loss to follow-up” to “deceased.” Drug resistance profiling via molecular assays will be performed exclusively in bacteriologically confirmed active TB cases.

### Statistical Analysis

Statistical analyses will be performed using SAS and R (R Foundation for Statistical Computing). Multiple imputation will be conducted to handle missing data, with additional inverse probability weighting applied for the nonintervention cohort to adjust for potential attrition bias. Continuous variables will be summarized as mean (SD) or median (IQR), as appropriate. Categorical variables will be summarized as counts and percentages.

The primary analysis will assess the noninferiority of the 1H_3_P_3_ regimen compared to the 3HR regimen in preventing active TB over the 24-month follow-up period, and the primary end point is the composite of bacteriologically confirmed or clinically diagnosed active TB. To account for the cluster randomized design and the inherent correlation within clusters, we will use a Cox proportional hazards regression model with shared frailty terms and exact likelihood estimation. Noninferiority of the 1H_3_P_3_ regimen relative to the 3HR regimen will be concluded if the analysis demonstrates that the 1H_3_P_3_ regimen does not experience a ≥20% relative reduction in protective efficacy for preventing active TB over the 24-month follow-up period. To enhance precision and address potential baseline imbalances despite randomization, the model will adjust for key prespecified covariates, such as age, sex, BMI, characteristics of the index case (smear or cavitation status), and cluster size. Outcomes will be assessed via 2 prespecified analyses with explicit definitions: the modified intention-to-treat population includes all randomized participants who received at least 1 dose of the study medication, analyzed by the assigned treatment group regardless of subsequent protocol deviations or treatment discontinuation; the per-protocol population includes all randomized participants who completed ≥90% of scheduled doses within 110% of the planned treatment duration without major protocol deviations (including use of prohibited concomitant anti-TB medications, enrollment despite exclusion criteria, or unblinding to outcome assessors). Prespecified subgroup analyses will examine treatment effect heterogeneity by age (13-17 years vs ≥18 years) and index case features (smear or cavitation status), tested through interaction terms in Cox models (interaction *P*<.10).

For secondary end points, all AEs, serious AEs (SAEs), and treatment discontinuations due to AEs will be documented. Group differences in AE proportions will be analyzed using the chi-square test or Fisher exact test (2-sided *α*=.05). Treatment completion is defined as consuming ≥90% of planned doses within 110% of the planned treatment duration (≥11 doses within 6 weeks for the 1H_3_P_3_ group and ≥81 doses within 16 weeks for the 3HR group). The 2-year cumulative incidence of active TB in the nonintervention cohort will be calculated using the Kaplan-Meier method, with 95% CI estimated. The protective efficacy of the 1H_3_P_3_ and 3HR regimens relative to the nonintervention cohort will be quantified as the risk reduction rate: 1–(intervention group incidence/nonintervention group incidence). The Fisher exact test will be used to compare incidence differences among the 3 cohorts.

All analyses concerning the PRO end point will be explicitly restricted to the subgroup of participants who complete the EuroQol 5-Dimensions 3-level questionnaire. The baseline characteristics of this PRO subgroup will be compared between the 2 arms to confirm that randomization balance was maintained. Any interpretation of PRO findings will explicitly acknowledge their exploratory nature and the fact that they are derived from a subset of the total study population. Trends in PRO metrics over time will be visualized using line graphs, with mean values and 95% CIs plotted to illustrate group-level changes. A mixed-effects model for repeated measures will be used to compare PRO differences between the 1H_3_P_3_ and 3HR groups across time points, with fixed effects including treatment group, assessment time point, treatment group×time point interaction, age, sex, BMI, and index case cavitation status, and a random participant-specific intercept to account for within-subject correlation from repeated assessments.

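### In the exploratory comparison with the nonintervention cohort, the Fisher exact test cannot use the Kaplan-Meier censoring or the attrition weights planned for that cohort, so its p-value need not agree with the protective-efficacy estimate

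*Protocol article*

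**What the plan says.** All of this is in the protocol article; the analysis plan is not shown.

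- **Missing data (Statistical Analysis).** The general rule is "Multiple imputation will be conducted to handle missing data", with no restriction to any cohort. The same sentence continues "with additional inverse probability weighting applied for the nonintervention cohort to adjust for potential attrition bias". Weighting is thus an addition to imputation and is named for one cohort only.
- **Incidence (Statistical Analysis, secondary end points).** "The 2-year cumulative incidence of active TB in the nonintervention cohort will be calculated using the Kaplan-Meier method, with 95% CI estimated".
- **Protective efficacy (same paragraph).** It is one minus a ratio, written as "1–(intervention group incidence/nonintervention group incidence" (final bracket omitted). No estimator is named for the numerator.
- **Test (same paragraph).** "The Fisher exact test will be used to compare incidence differences among the 3 cohorts".
- **Randomized comparison (Statistical Analysis).** For the primary end point, "we will use a Cox proportional hazards regression model with shared frailty terms and exact likelihood estimation".
- **Attrition (Randomization and Sample Size Calculation).** "Accounting for a 10% attrition rate to mitigate the impact of loss to follow-up on statistical power and outcome validity", each arm enrolls 1760. No attrition figure or size is given for the nonintervention cohort.
- **Status (Study Objectives and End points).** The comparison with the nonintervention cohort is listed under the fourth secondary objective and is labelled exploratory, both there and in the paragraph on end points.

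**The concern.** The protocol recognises that attrition may bias the nonintervention incidence, and it plans a censoring-aware estimator and weights to deal with this. The one test it names for the three-cohort comparison can use neither. A Fisher exact test conditions on the margins of an integer table: each person is in or out of the table and has TB or does not.

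Two consequences follow. The p-value and the efficacy estimate answer slightly different questions about the same people, and they may diverge when dropout is unequal. And because only one side of the efficacy ratio has a named estimator, the analyst could choose a different one for the other side.

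Unequal retention is plausible. Arm participants have in-person treatment visits, medication diaries and peer coordinators, while the nonintervention cohort consists of people who declined the trial. These efficacy figures would attract attention, because protective efficacy is also the scale on which the protocol expresses its noninferiority margin.

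**Working it through.** **Inputs.** From Randomization and Sample Size Calculation: 2-year incidence 7% untreated and 2.1% on either regimen; efficacy 1 − 2.1/7 = 70.0%; arm attrition 10%. Assumed here: constant hazard, non-informative loss spread evenly over 24 months, no imputed outcomes, and nonintervention loss of 20%, 30% or 40%.

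**The plan's own attrition figure.** 1584 / (1 − 0.10) = 1760 per arm, which reproduces exactly.

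**Formulas.** For 24-month risk p and fraction lost L, put λ = −ln(1 − p). The average risk accrued before an evenly spread loss time is m = 1 − p/λ. The proportion seen to develop TB is E = (1 − L)p + L·m.
- Lost people kept in the denominator as TB-free: raw incidence = E.
- People lost before TB dropped: raw incidence = E / [1 − L(1 − m)].

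**Arms, p = 0.021, L = 10%.** λ = 0.021224 and m = 0.010537. E = 0.9 × 0.021 + 0.1 × 0.010537 = 0.01995. Dropped: 0.01995 / (1 − 0.1 × 0.98946) = 0.02215.

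**Nonintervention, p = 0.07.** λ = 0.072571 and m = 0.035423.

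| Assumed loss | Raw incidence, kept | Raw incidence, dropped | Efficacy, kept | Efficacy, dropped |
|---|---|---|---|---|
| 20% | 6.31% | 7.82% | 68.4% | 71.7% |
| 30% | 5.96% | 8.39% | 66.5% | 73.6% |
| 40% | 5.62% | 9.15% | 64.5% | 75.8% |

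Each efficacy is 1 − (arm raw incidence / nonintervention raw incidence), with the arms at 10% loss and the same kept-or-dropped rule on both sides. Example: 1 − 0.01995/0.06309 = 68.4%.

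**Raw arm proportion over Kaplan-Meier nonintervention incidence.** With lost people kept, 1 − 0.01995/0.07 = 71.5% at 10% arm loss. At an assumed 20% arm loss, E = 0.01891 and efficacy is 73.0%. With lost people dropped at 10% arm loss, 1 − 0.02215/0.07 = 68.4%. The shift is about 1.5 points either way, and its direction depends on a rule that the article does not state.

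**Sensitivity to the dropout pattern.** With exponential dropout of rate g = −ln(1 − L), the raw proportion with lost people kept is λ/(λ + g) × [1 − exp(−(λ + g))]. At 10% arm loss this gives 1.99% in the arms and 71.5% for the mixed ratio. For raw counts at 20%, 30% and 40% nonintervention loss it gives 68.3%, 66.2% and 63.7%.

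**Same estimator on all sides.** Under non-informative loss, Kaplan-Meier targets 2.1% and 7%, and efficacy returns to 70.0%.

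**Scale against sampling error.** The nonintervention size is not given, so 200 and 1000 are assumed; clustering is ignored, and 1760 per arm gives 0.021 × 1760 ≈ 37 events.
- With 200 (14 events), SE of the log ratio = √(1/14 − 1/200 + 1/37 − 1/1760) ≈ 0.305, so the 95% interval for efficacy is about 45% to 83%.
- With 1000 (70 events), SE ≈ 0.199 and the interval is about 56% to 80%.

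**The case against.** The strongest reply is that multiple imputation is stated for missing data without naming a cohort. If 24-month TB status is imputed, every lost person has an outcome in each completed dataset and a Fisher test can be run on each. A reader might infer from the Fisher sentence that the p-value ignores attrition, or that each lost person must be counted as TB-free or dropped. The text does not support either reading. How p-values would be pooled is a detail for the analysis plan. What remains is narrower: even on imputed data, a Fisher test cannot carry the additional weights. Planning Kaplan-Meier and attrition weights also suggests, without proving it, that some follow-up will be treated as censored rather than imputed.

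Second, a reader might infer that the efficacy ratio mixes a raw proportion with a Kaplan-Meier estimate. The article does not say so. The arms' estimator is unnamed, the end point is a 24-month cumulative incidence, and the arms are otherwise analysed with a time-to-event model. The 71.5% is therefore conditional.

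Third, the larger shifts rest on nonintervention losses that appear nowhere in the protocol, and on a raw-count efficacy that the plan does not say it will report. Under non-informative loss the test's conclusion is also unlikely to change. With an assumed 300 in the nonintervention cohort, 40% lost there and 10% lost in one arm, a pairwise Fisher test on 16/300 against 35/1760 still gives p ≈ 0.002.

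Fourth, giving extra weighting to the non-randomized cohort is not wrong in itself. These points limit the size and the wording of the concern. They do not remove the mismatch between the stated test and the stated estimate.

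**Conclusion.** The concern holds in a limited form. The stated test cannot use the censoring and weighting stated for one of the three cohorts it compares, so its p-value need not agree with the efficacy estimate.

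Only the shift of about 1.5 points uses an attrition figure from the protocol. It assumes non-informative loss, no imputed outcomes and a raw proportion in the arms, and it is small against the sampling error of this comparison. The ranges of about 64% to 68% and 72% to 76% illustrate what raw counts would imply under assumed nonintervention loss. Informative dropout could make the discrepancy larger, but the documents give no basis for a figure.

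A reader might set these shifts against the 14 points (70% to 56%) that the noninferiority criterion allows. That benchmark does not apply here. Noninferiority is judged from the Cox shared-frailty model in the randomized arms, which handles censoring and is not touched by this point. Because the comparison is exploratory, this is a change to consider rather than one the trial's conclusion depends on.

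**What to change.** Estimate 24-month incidence in all three groups with one estimator: Kaplan-Meier with inverse-probability-of-censoring weights built from the same covariates. Form each regimen's protective efficacy from those estimates. Replace the Fisher test with a confidence interval and test for each regimen's contrast with nonintervention, obtained by bootstrap resampling of index-case clusters with the weights refitted in each resample. State whether multiple imputation covers TB status after loss or only other variables, so that the same loss is not handled twice.

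The cost is wording in the analysis plan and a little code, with no new data. The intervals may be wider than a raw-count test would suggest. The protocol places analysis after the 2-year follow-up, so the change can be made beforehand.
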